## Abstract

**Background:**

Stroke is the third leading cause of death in developed countries and the leading cause of long-term disability worldwide. A series of national stroke audits in the UK highlighted the differences in stroke care between hospitals. The study aims to describe variation in outcomes following stroke and to identify the characteristics of services that are associated with better outcomes, after accounting for case mix differences and individual prognostic factors.

**Methods/Design:**

We will conduct a cohort study in eight acute NHS trusts within East of England, with at least one year of follow-up after stroke. The study population will be a systematically selected representative sample of patients admitted with stroke during the study period, recruited within each hospital. We will collect individual patient data on prognostic characteristics, health care received, outcomes and costs of care and we will also record relevant characteristics of each provider organisation. The determinants of one year outcome including patient reported outcome will be assessed statistically with proportional hazards regression models. Self (or proxy) completed EuroQol (EQ-5D) questionnaires will measure quality of life at baseline and follow-up for cost utility analyses.

**Discussion:**

This study will provide observational data about health service factors associated with variations in patient outcomes and health care costs following hospital admission for acute stroke. This will form the basis for future RCTs by identifying promising health service interventions, assessing the feasibility of recruiting and following up trial patients, and provide evidence about frequency and variances in outcomes, and intra-cluster correlation of outcomes, for sample size calculations. The results will inform clinicians, public, service providers, commissioners and policy makers to drive further improvement in health services which will bring direct benefit to the patients.

## Background

Stroke is the third leading cause of mortality and the number one cause of long-term disability in the UK. More than 150,000 people suffer a stroke in the UK each year [1]. It costs the NHS approximately £ 7 billion per annum [2]. Stroke incidence rises sharply with age and despite better primary and secondary preventative measures, the total number of strokes is set to rise in the UK [3]. Nevertheless, stroke care in UK is far from ideal: patients having a worse outcome in terms of death and dependency than many other European countries [4-6], at least in part due to differences in care provided [7]. There is also variation in outcome between different localities within the UK [8-11], these local differences being highlighted in the most recent publication of the National Sentinel Stroke Audit in 2009 [12]. These differnces probably arise as a result of substantial variations in how the stroke services are provided across the UK. Examples of such differences are access to neurovascular/neurosurgical service, early supported discharge, and stroke specialist on call rota for thrombolysis. The presence or absence of variations in stroke outcomes as a result of variation in care and how much the observed variations in patients' outcomes including patient reported outcome measure (PROM) are determined by the differences in service delivery have not been examined previously.

We hypothesise that variation in patient outcomes including mortality, length of stay, institutionalisation rate, and patient reported outcomes between care providers can partly be explained by the different ways in which stroke services are delivered. The main objectives of the study are (1) to describe variation in outcomes following stroke and to identify the characteristics of services that are associated with better outcomes after accounting for case mix differences and individual prognostic factors, and (2) to obtain preliminary data to identify sample size and inform future pragmatic real world setting RCTs in the area of health service delivery in stroke.

## Methods/Design

A prospective cohort study will be conducted to identify characteristics of services that are associated with the best outcomes including patient reported outcomes, taking into account case-mix and patients' prognostic features. The study will consist of two components (1) consecutive stroke admissions in selected months (a total of 8 months) and (2) a prospective study of patient reported outcome in some of these selected months.

### Sample Population

For the first component, the sample population will be stroke patients who are admitted to any of the hospitals within the Anglia region of Stroke & Heart Clinical Network between October 2009 and September 2011. Baseline data are already recorded, prior to the study commencement, as part of routine clinical data collection by Anglia Stroke Clinical Network (as described in detail below). The study sample will be a systematically selected sample (every third month) rather than a consecutive cohort of patients admitted to eight acute NHS hospital trusts. Therefore, this is not a consecutive case study; instead it seeks to be representative of the catchment population of the hospital and has taken into account the seasonal variation in stroke incidence and outcome [13].

For the patient reported outcome component of the study the following inclusion and exclusion criteria will be used. Inclusion criteria are (1) age > = 18 years, (2) admitted to hospital with stroke (diagnosed by stroke physicians) during the study months, (3) able to provide informed consent or patient's personal consultee agrees to study participation. Exclusion criteria include (1) age <18 years, (2) patients with pre-existing diagnosis of dementia (for PROM component only).

The Anglia Stroke Network was funded through the NHS Improvement Programme, following the publication of the National Stroke Strategy in December 2007. The Network was established in April 2008 to support the development of stroke services in Norfolk, Suffolk and Cambridgeshire regions. Since its inception, the Network regularly collected data to capture clinical service activities of the eight acute hospital trusts in the Network for the purpose of monitoring of services benchmarked by National targets and guidance from National Institute of Health & Clinical Excellence (NICE) in England and Wales. Data collection commenced in January 2009 and involves the individual trusts collecting clinical data which is fed back to the network by monthly reports. The total number of strokes admitted to the 8 acute trusts within the Network is approximately 4,000 per annum in 2009. The stroke cases were identified prospectively data were collected by the clinical team who looked after the patients and anonymised raw clinical data were sent to the network on monthly basis. The network collates and analyses the data for above mentioned purposes.

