### Patient Reported Outcome Measures (PROM)

PROM will consist of (1) Stroke Impact Scale, (2) health related quality of life: EQ-5 D at one year in those who completed questionnaire at the baseline, (3) modified RANKIN, (4) Barthel score and (5) health service use.

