#### Outcome

As the National Institute of Health and Clinical Excellence [18] recommends use of the EQ-5 D [17] within cost-effectiveness analysis this will be our primary measure within the economic analyses. EQ-5 D data will be collected at two University Hospitals and two district general hospitals within the clinical network. We will use "mapping" strategy to estimate the cost-effectiveness analyses across the region. The use of mapping, where scores from a condition-specific (non preference-based) measure are 'converted' into a utility (preference-based) score using a pre-defined formulae, has been advocated (in certain instances) by the UK National Institute of Health and Clinical Excellence (NICE) [18], and has been used to estimate the utility scores, and in turn cost-effectiveness, of a number of health care interventions [19]. Mapping presents the possibility of not asking all participants to complete the EQ-5 D. In this study we propose to take advantage of this by developing a mapping algorithm based on the response from participants participating in this component to predict the EQ-5 D for participants in retrospective cohorts and those who did not participate in PROM component.

Because the quality of life measure (EQ-5D) which can be used to estimate health utility and calculate QALYs (Quality Adjusted Life Years) for economic evaluation is outside the remit of routine data collection and cannot be done retrospectively, we will collect EQ-5 D data in only the second year of the study (October 2010 and January, April and July 2011 cohorts and one year follow up data to be collected September and December 2011, and March and June 2012) in those who provide informed consent to the study (we estimate that the sample will be approximately 15-20% of the whole sample after excluding the one year pre-study period (between October 2009-September 2010) and after taking into account of refusal rate (estimated ~ 30%) in trusts with Stroke or Comprehensive Local Research Network Research Nurses.

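### Mapped EQ-5D is applied to patients with pre-existing dementia, but no such patient can contribute to the mapping, so their share of the region-wide cost-utility result is unsupported extrapolation

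*Protocol article*

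**What the plan says.** All places are in the protocol article.

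- **Sample Population** lists as an exclusion "patients with pre-existing diagnosis of dementia (for PROM component only". The restriction applies to that component alone. Patients with a prior dementia diagnosis remain in the main cohort, which is meant to represent each hospital's catchment.
- **Patient Reported Outcome Measures (PROM)** makes EQ-5D a PROM item: "EQ-5 D at one year in those who completed questionnaire at the baseline".
- **Outcome** (under Economic evaluation) limits collection in time, "we will collect EQ-5 D data in only the second year of the study", and in place: "EQ-5 D data will be collected at two University Hospitals and two district general hospitals within the clinical network". It also limits collection to patients who consent.
- The same section describes "developing a mapping algorithm based on the response from participants participating in this component" and gives its purpose: "to predict the EQ-5 D for participants in retrospective cohorts and those who did not participate in PROM component". The stated aim is cost-effectiveness for the whole region. No exception is made for patients with dementia.
- **Statistical analysis** adds that missing EQ-5D will be imputed from the patient's other prognostic characteristics. **Economic Analysis** promises sensitivity analysis of key assumptions without naming any. The limitations in the **Discussion** cover confounding and causal interpretation only.

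**The concern.** The exclusion and the prediction target do not fit together. A mapping algorithm can learn only from the patients who answered. By rule, no respondent has pre-existing dementia, so a dementia term in the algorithm would have no estimable coefficient. Each patient with dementia receives the utility of a patient without it who looks alike on the other inputs. Whether that value is right cannot be checked within the study.

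Costs are affected differently. Resource use is recorded for patients during follow-up, so for patients with dementia the cost-effectiveness ratio would combine recorded costs with benefits borrowed from other patients. If a service improves survival, the life-years gained by these patients are also valued at an unsupported utility. The Discussion expects commissioners to use the results in purchasing, so the population that the QALY figures rest on should be stated.

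**Working it through.** **1. How much of the cohort is predicted.** The article's cohort size reproduces: 0.30 × 4,000 × 2 = 2,400. It puts the EQ-5D sample at about 15-20% of the whole. Year two covers 4 of the 8 study months (0.5) and refusal is about 30% (0.70 remain). The four hospitals' share of admissions, s, is not given.

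- Fraction = 0.5 × s × 0.70
- s = 0.50 (assumed): 17.5%, or 420 patients
- s = 0.43 to 0.57 (assumed): 15.1% to 19.9%, or about 361 to 479 patients

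The stated range thus follows from year, hospital and refusal, with no visible allowance for the dementia exclusion. The other 80-85% (1,920 to 2,040 of 2,400) would have predicted EQ-5D.

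**2. Patients with dementia among those predicted.** Observed EQ-5D in this group is zero by design. The documents give no prevalence d, so a range is assumed. At d = 5%, 120 patients are affected, or 0.05/0.85 to 0.05/0.80 = 5.9% to 6.3% of those predicted. At d = 20%, 480 are affected, or 0.20/0.85 to 0.20/0.80 = 23.5% to 25%.

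**3. Shift in cohort mean utility.** Shift = d × b, where b is the average over-prediction in patients with dementia (assumed).

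| d | patients | b = 0.05 | b = 0.10 | b = 0.20 |
|---|---|---|---|---|
| 5% | 120 | 0.0025 | 0.005 | 0.01 |
| 10% | 240 | 0.005 | 0.01 | 0.02 |
| 15% | 360 | 0.0075 | 0.015 | 0.03 |
| 20% | 480 | 0.01 | 0.02 | 0.04 |

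**4. Shift in a crude difference between two services.** Shift = g × b, where g is the gap in dementia prevalence between the services (assumed).

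- g = 5 points: 0.05 × 0.05 = 0.0025 to 0.05 × 0.20 = 0.01
- g = 10 points: 0.10 × 0.05 = 0.005 to 0.10 × 0.20 = 0.02

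**5. Effect of deaths.** Patients dead at one year need no predicted one-year utility. With the 20-30% mortality used in Sample size, and assuming the same mortality in patients with dementia, a shift of 0.02 becomes 0.02 × 0.80 = 0.016 to 0.02 × 0.70 = 0.014 at one year.

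**6. Effect of case-mix adjustment.** A constant over-prediction b largely cancels from an adjusted service contrast if dementia is among the covariates. It does not cancel from mean QALYs, from the value placed on extra survival, or where service effects differ by dementia status.

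**The case against.** The strongest reply is that the effect on a comparison of services may be small. Mapping inputs that reflect function or dependency could carry much of dementia's effect and leave only a residual. The study's objectives require case mix to be accounted for, and Economic evaluation states adjustment when it describes incremental cost. Compared services may also pool several trusts, which narrows any prevalence gap. All of this stands as a limit on size. It does not supply the missing information: the residual can be neither estimated nor checked, and Rankin and Barthel are themselves listed as PROM items, so they are not shown to be available for non-participants.

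It can also be said that algorithm inputs and detailed sensitivity analyses belong in a fuller document. That is fair, and their absence is not the point here. The article itself states both the exclusion and the prediction target, and the mismatch follows from those two statements whatever the inputs are.

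A reader might infer three stronger things that the documents do not support:

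- That the consultee route, "able to provide informed consent or patient's personal consultee agrees to study participation", and proxy completion of EQ-5D contradict the exclusion. They do not: both can serve patients incapacitated by the stroke itself.
- That nothing is known about patients with dementia. Only EQ-5D is absent; baseline, mortality and resource-use data are planned for them.
- That services will show a false utility difference of 0.02. That needs both a 10-point prevalence gap and a 0.20 over-prediction, with no adjustment. The documents give neither figure, and the direction also rests on an assumption.

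**Conclusion.** The point holds as a limit on what the economic analysis can support. Followed as written, the plan assigns patients with pre-existing dementia utilities that no EQ-5D response from such a patient informs, and includes them in a region-wide result. Neither the imputation from prognostic characteristics nor an unspecified sensitivity analysis corrects this.

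The error is probably upward if dementia lowers utility beyond what the inputs capture, but its size cannot be derived from the documents. Under the assumed ranges, mean utility moves by about 0.0025-0.04 and a crude service difference by about 0.0025-0.02, with smaller effects after deaths and adjustment. The point concerns one subgroup in the economic analysis of an exploratory study; the primary mortality comparison is unaffected. It is worth correcting because the remedy is cheap and changes the population for which the cost-utility result can be claimed.

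**What to change.** Amend the Outcome and Economic Analysis sections as follows:

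1. Record pre-existing dementia as a yes/no item for all cohorts, from the case records that clinical teams already retrieve for baseline measures.
2. State that the mapped EQ-5D is supported by data only for patients without pre-existing dementia.
3. Include the flag in the case-mix adjustment of both costs and effects.
4. Report cost-utility results in two ways: excluding these patients, and including them over a stated range of utility decrements.

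The cost is one extra baseline item, some added analysis and a more cautious region-wide claim. Reporting both results avoids making a narrower population the sole headline, which would sit poorly with the aim of representing the catchment and would alter costs as well as utilities. The eligibility criteria need not change.

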### Sample size

Since this is an exploratory study designed to provide information for further analytic research, sample size will be determined partly pragmatically rather than on particular hypothesis tests. For illustration purposes, a total sample of 2264 patients would provide 80% power to detect a constant Hazard ratio (HR) of 0.76 for one-year mortality between two groups of roughly equal size, based on the log-rank test. This assumes a 20% one-year mortality rate in the reference group, no loss to follow-up before one year and 2-sided type I error of 5%. If one-year mortality is 30%, then 2264 patients would provide 76% power to detect a HR of 0.81.

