### Outcome measurements

Primary outcome of the study will be one year mortality comparison between services with different characteristics. The secondary outcomes will include (1) final discharge destination (good or poor outcome) [16], (2) length of acute hospital stay, (3) length of stay in rehabilitation, (4) complications during acute and rehab-hospital stay and significant procedures (e.g. aspiration pneumonia, myocardial infarction), (5) readmissions, (6) composite cardiovascular events (recurrent TIA/Stroke/Acute Coronary Syndrome, Myocardial infarction).

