### Statistical analysis

Quantitative data will be analysed by multivariate Cox-proportional hazards to examine the relationships between different aspects of health services and time to death, adjusting for prognostic characteristics. Multiple logistic or linear regression models will be constructed as appropriate for dichotomised and continuous outcome variables respectively. T tests for normally distributed data and Mann-Whitney U tests for non-normally distributed data will be used to compare continuous outcomes. Volume-outcome relationships will be investigated. Missing prognostic and EQ-5 D data will be imputed, based on each patient's other prognostic characteristics. Clustering of data by hospital trust will be investigated and, if necessary, taken into account, and intra-class correlation coefficients calculated to inform future research.

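### The stated 80% and 76% power assume independent patients, so they do not apply to hospital-level service characteristics compared across eight trusts

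*Protocol article*

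**What the plan says.** The Sample size section presents the study as exploratory, with numbers set partly on pragmatic grounds. As an illustration it states "a total sample of 2264 patients would provide 80% power to detect a constant Hazard ratio (HR) of 0.76", for two groups of about equal size compared by a log-rank test. Its assumptions are listed: "This assumes a 20% one-year mortality rate in the reference group", complete follow-up to one year and a two-sided 5% test. A second scenario follows: "If one-year mortality is 30%, then 2264 patients would provide 76% power to detect a HR of 0.81". It mentions neither clustering nor the number of trusts.

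The primary outcome is a "one year mortality comparison between services with different characteristics" (Outcome measurements). Patients come from every third month of admissions rather than from a consecutive "cohort of patients admitted to eight acute NHS hospital trusts" (Sample Population). The Plan of investigation lists service characteristics under two headings:

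- **Hospital level:** staffing, university or district general status, distance from the tertiary centre, on-site surgery and neuro ITU, monitoring beds, on-call rota, and compliance with NICE guidelines.
- **Patient level:** thrombolysis and CT, and medication.

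The Statistical analysis section says that clustering by trust will be examined and allowed for if needed, with "intra-class correlation coefficients calculated to inform future research".

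**The concern.** A log-rank power calculation on 2264 patients treats each patient as a separate piece of information about the contrast. That is reasonable when the exposure differs between patients in the same trust. When every patient in a trust has the same value, as with university status, the contrast is between groups of trusts. At best it is four against four, and any difference between trusts in underlying mortality adds to its variance.

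The study cannot take independence for granted. Its hypothesis is that outcomes vary between providers, and one of its aims is to supply intra-cluster correlations for later sample size calculations. Its own power statement leaves them out.

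At stake is the reading of a null result. The Discussion expects commissioners to use the findings when deciding which service structures to buy. A reader who believes that HR 0.76 was detectable with 80% power could take a null finding for a hospital feature as evidence that the feature does not matter.

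**Working it through.** **Inputs from the article.** N = 2264; two groups of about equal size; two-sided 5%; no loss to follow-up; HR 0.76 at 20% reference mortality; HR 0.81 at 30%, also taken as the reference rate; eight trusts, so 2264 / 8 = 283 patients per trust on average.

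**Assumptions made here.** The article gives no ICC, so 0.002, 0.005 and 0.01 are used. At about 18% mortality these correspond to a between-trust standard deviation of √(ICC × 0.178 × 0.822), or about 1.7 to 3.8 percentage points at the two ends. Trusts are of equal size, split four against four, and the characteristic is constant within each trust.

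**Step 1: reproduce the stated power with independent patients.** Mortality in the better group is p1 = 1 − (1 − p0)^HR. Deaths are D = (N/2)(p0 + p1). Power (Schoenfeld) is Φ(√(D/4) × |ln HR| − 1.96).

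- HR 0.76, p0 = 0.20: p1 = 0.156, D = 1132 × 0.356 ≈ 403. √(403/4) × 0.2744 = 2.75, so power is 78.7% (stated: 80%).
- HR 0.81, p0 = 0.30: p1 = 0.251, D = 1132 × 0.551 ≈ 624. √(624/4) × 0.2107 = 2.63, so power is 74.9% (stated: 76%).

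Both are within two points of the stated figures, with no allowance for clustering.

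**Step 2: add the design effect.** DE = 1 + (283 − 1) × ICC, and D is replaced by D/DE. This is the usual approximation. The t column uses a noncentral t distribution on 8 − 2 = 6 degrees of freedom, because a contrast between trusts has only eight units.

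| Assumed ICC | DE | HR 0.76 at 20%: normal | HR 0.76 at 20%: t, 6 df | HR 0.81 at 30%: normal | HR 0.81 at 30%: t, 6 df |
|---|---|---|---|---|---|
| 0 | 1.00 | 79% | 63% | 75% | 60% |
| 0.002 | 1.56 | 60% | 46% | 56% | 42% |
| 0.005 | 2.41 | 43% | 32% | 40% | 30% |
| 0.01 | 3.82 | 29% | 22% | 27% | 21% |

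Example: at ICC 0.005, √(403/4/2.41) × 0.2744 = 1.77, and Φ(1.77 − 1.96) ≈ 43%.

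**Step 3: HR detectable with 80% power at 20% reference mortality.** Deaths are recalculated for each HR, since fewer occur as the HR falls.

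| Assumed ICC | Normal | t, 6 df |
|---|---|---|
| 0.002 | 0.70 | 0.65 |
| 0.005 | 0.64 | 0.58 |
| 0.01 | 0.56 | 0.49 |

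**The case against.** The strongest reply is that the calculation claims little. It is labelled an illustration, the study is called exploratory, and the cohort size follows from sampling every third month rather than from this calculation. The section does not say that its two groups are sets of hospitals. The Discussion disclaims causal conclusions and points to later trials. All of this stands, and it lowers the severity. It does not make the figure fit: this is the only power statement in the article, and for most listed characteristics the primary comparison is not one between independent patients.

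The analysis plan also allows for clustering if needed. That can correct standard errors, but it cannot restore the power quoted.

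The size of the loss is uncertain. The ICC is an assumption, and estimating it is one of the study's aims. Case-mix adjustment may lower it. Part of the drop comes from the 6-df reference rather than from the ICC: at ICC 0 that reference alone takes 79% to 63%. Both references are therefore shown.

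Three stronger readings are tempting but not supported:

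- A reader might infer that the arithmetic is wrong. It reproduces; the difficulty is the unit of analysis.
- A reader might infer that every comparison falls short of the stated power. Thrombolysis, CT and medication can vary within a trust, and for balanced contrasts of that kind the stated power may be nearly right.
- A reader might infer that all hospital-level characteristics are constant within a trust throughout. The article does not say that staffing, rota or monitoring beds stayed the same over the two years sampled. The tables hold for those that did.

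**Conclusion.** The point holds for hospital-level characteristics that are constant within a trust. For these, any positive ICC puts power below the stated 80% and 76%. Under the assumptions above, power for HR 0.76 lies between about 60% and 29% (normal) or 46% and 22% (6 df), and effects would need to be clearly larger than HR 0.76 to be detected with 80% power. The direction does not depend on the assumed ICC; the exact size does. This is a unit-of-analysis problem of moderate severity, because the study is labelled exploratory and nothing in its conduct rests on the figure.

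**What to change.** Amend the Sample size paragraph in three ways:

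1. State that the 80% and 76% assume independent patients and apply only to patient-level characteristics that vary within trusts, such as thrombolysis, CT and medication.
2. For hospital-level characteristics, give power or detectable HR for eight trusts over an ICC range that is stated and labelled as assumed. Name the reference distribution, and note that case-mix adjustment may reduce the ICC.
3. Say that a null result for a hospital-level characteristic is not evidence of no effect.

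The cost is rewording one paragraph. No more patients or data are needed. The downside is a less favourable stated power for the hospital-level comparisons.
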